### Sample size

The sample size has been calculated considering a relevant post-intervention average difference of 10 points on a 100-point evaluation questionnaire between groups and a standard deviation of 0.5 [31]. Assuming an alpha error of 0.05 and a beta error of 0.10, 84 subjects are required for each group. Because randomization is performed by clusters, the sample size has been adjusted to take into account the design effect. Thus, for an average of 30 residents per teaching unit, and an intraclass correlation coefficient (ICC) of 0.03 (literature shows an ICC of 0–0.052 for similar teaching interventions) [32], a design effect of 1.87 has been obtained. With these assumptions, and expecting a 25 % loss to follow-up after a 6-month period, the required sample size is 394 (197 per group).

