### Competence assessment in both groups

An evaluation of baseline competence will be performed for each guideline prior to its presentation, and two further tests will be carried out at 1 and 6 months after the intervention. The test will evaluate the level of knowledge and decision-making in relation to ten hypothetical cases of routine clinical practice that are related to the content of each guideline; the test will yield a maximum score of 100 and will be completed within 45 min.

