### Variables

The primary outcome variable will be the participant score obtained in the test assessing competence 1 month after the intervention. The secondary outcome variable

[figure not shown]

will be the competence test score 6 months after the intervention.

(a) Teaching unit variables

- Sociodemographic characteristics of the program director and technician: sex, age, specialty,

academic level, time spent in that position, experience in elaborating guidelines or recommendation, and training in EBM

- Unit characteristics: total number of residents (R1, R2, R3, R4); position of the teaching unit in the ranking, obtaining residency positions in

[figure not shown]

|               |                                                                                                                                                                                                                                   |
|---------------|-----------------------------------------------------------------------------------------------------------------------------------------------------------------------------------------------------------------------------------|
| 1             | Initial 60-minute session comprising the following content: Clinical Practice Guideline; information on and presentation of the GuiaSalud website, and a link to the guidelines library; instructions for downloading guidelines. |
| a             | Family Medicine Teaching Units and Residents Doctors baseline variables                                                                                                                                                           |
| b             | CPG Recommendations Baseline Competence Test                                                                                                                                                                                      |
| RANDOMIZATION |                                                                                                                                                                                                                                   |
| c             | Routine dissemination of CPG recommendations by mail.                                                                                                                                                                             |

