**Statistical analysis**

1. Descriptive and exploratory analysis: This analysis will include participants' baseline characteristics and outcomes, means and standard deviations (SD) for

continuous variables, and proportions for categorical variables with its corresponding 95 % confidence interval (CI). Baseline comparison between the two groups in terms of the score competence test and descriptive and prognostic factors will be performed by bi-variant statistical tests.

2. Inferential analysis: Student's *t* test with a 95 % CI will be performed to compare both groups' results in the competence test in terms of score at baseline and 1- and 6-month post-implementation of each CPG recommendation.
3. Multilevel analysis: a mixed model will be constructed for the evaluation of the influence of the teaching unit on the effectiveness of the intervention. The dependent variable will be the score obtained in the competence test. The model will consist of two levels: resident doctors will comprise the first level and the teaching unit will comprise the second.
4. Dropouts and missing data

Because this trial will use an online system to allocate participants and collect baseline and outcome data, participants can leave the study at any time. To minimize the possibility of dropouts and missing data, several strategies will be considered. If a participant leaves the study before randomization, the participant will be excluded and we will not consider this as missing participant data.

All statistical tests will be performed with an intention-to-treat analysis. The last observation carried forward will be used for missing data imputation, and there will be report analyses with and without imputation [36].

Significance will be set at  $p < .05$ . Calculations will be performed using MLwiN and STATA v.12 software with specific related modules.

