### Discussion

Teaching units from across Spain will participate in this clinical trial, which anticipates high external outcome validity. Additionally, this intervention might provide information to consider for training in other specialties.

The intervention to be assessed cannot be masked, which could influence its effect. Because there is a possibility of contamination bias among residents, randomization by clusters has been proposed, under the assumption that the number of clusters will be sufficient for each group. Geographic dispersion of the teaching units reduces the possibility of contamination.

Teaching strategies are complex interventions; the design of educational games as an interactive, self-learning application allows for standardization of the intervention.

The considerable variability foreseen between teaching units regarding training in CPGs could imply that some residents have better training with some of these CPGs, which could result in a lack of improvement in these residents' decision-making scores (competency test score). However, this possibility will be adjusted using the training variables of both the teaching units and the residents.

To evaluate the intervention's effectiveness, the primary measurement will take place 1 month after implementation; at this time, our primary objective will be to confirm the effectiveness of the e-learning EDUCAGUIA strategy as a learning tool. Its effect at 6 months after the intervention might not remain, which would lead to a study on the effectiveness of reinforcement interventions. Measuring the primary response at 6 months was considered an option, but the characteristics of training during residency periods make it possible for the residents to acquire the knowledge and abilities of the intervention during rotations or other courses within that time period, thus hindering the isolation of the intervention effect.

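### Last observation carried forward (LOCF) gives residents missing at 1 month their pre-intervention score, and neither the imputed nor the unimputed analysis is named as primary; the bias depends on who is lost and when

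*Protocol*

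**What the plan says.** All references are to the Protocol.

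- **Missing data** (Statistical analysis, item 4): "All statistical tests will be performed with an intention-to-treat analysis". The next sentence reads: "The last observation carried forward will be used for missing data imputation, and there will be report analyses with and without imputation". Nothing says which of the two results leads.
- **Test schedule** (Competence assessment in both groups): a first test measures each resident before the guideline is introduced. After that, "two further tests will be carried out at 1 and 6 months after the intervention". No other scores are planned.
- **Outcomes** (Variables): "The primary outcome variable will be the participant score obtained in the test assessing competence 1 month after the intervention". The secondary outcome "will be the competence test score 6 months after the intervention".
- **Expected loss** (Sample size): the calculation is made "expecting a 25 % loss to follow-up after a 6-month period". No figure is given for loss at 1 month.
- **Expected course** (Discussion): "Its effect at 6 months after the intervention might not remain". The same paragraph says that residents may pick up the same competences from rotations or other courses in the meantime.
- **Model** (Statistical analysis, item 3): a mixed model with two levels, residents within teaching units. Item 2 adds Student's t tests at each time point.

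**The concern.** LOCF is only as good as the assumption that a score would not have changed since it was last measured. Here that assumption conflicts with the purpose of the trial and with its own Discussion.

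For the primary outcome, the only earlier observation is the test taken before the guideline is presented. Carrying it forward assumes no learning in anyone missing, in a trial that asks whether learning took place. For the 6-month outcome, a resident who took the 1-month test is assumed to have neither forgotten nor learned anything since. The Discussion expects that either may happen. A resident who missed both later tests again receives the baseline score.

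Two things are at stake. The 1-month estimate may differ from the true effect by an amount set by the pattern of loss. At 6 months, decay may be partly hidden, and the Discussion says that a lost effect would lead to a study of reinforcement. LOCF also treats filled-in values as if they had been observed. Because neither analysis is named as primary, the two reported results may disagree with no stated rule for choosing between them.

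**Working it through.** **Inputs.** From Sample size: difference 10 points on a 100-point scale, alpha 0.05, power 90%, 84 per group before adjustment, 30 residents per unit, ICC 0.03, design effect 1.87, 25% loss by 6 months, 197 per group.

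Assumptions:
- SD of 20 points. The Protocol prints 0.5; a standardised effect of 0.5, that is 10/20, reproduces the 84.
- Two-sided test.
- Loss at 1 month (m1) between 0 and 25%.
- Balanced baselines, and loss unrelated to outcome.
- SD unchanged by LOCF.

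**Step 1: reproduce the plan's figure.** n = 2 × [20 × (1.960 + 1.282)/10]² = 84.06, printed as 84. Design effect = 1 + 29 × 0.03 = 1.87. Then 84 × 1.87 = 157.08, and 157.08 × 1.25 = 196.35, rounded up to 197. The stated sample size reproduces.

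**Step 2: 1-month score under LOCF.** Missing residents contribute a gain of zero, so

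estimate = (1 − m_I) × gain_I − (1 − m_C) × gain_C,

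where I is the intervention arm and C the control arm. With equal loss m1 this is (1 − m1) × 10.

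Power with all 197 per group counted = Φ[(estimate/20) × √(197/1.87/2) − 1.96]. At 25% loss: (7.5/20) × 7.258 − 1.96 = 0.762, and Φ(0.762) = 0.777.

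For comparison, the analysis of observed scores keeps 10 points with 197 × (1 − m1) residents per group and a design effect of 1 + (30 × (1 − m1) − 1) × 0.03.

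**Step 3: 6-month score under LOCF.** Take total loss m6 = 25%, with residents lost by month 1 staying lost (monotone loss) and equal loss in both arms:

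estimate = (1 − m6) × δ6 + (m6 − m1) × δ1,

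where δ1 = 10 is the true 1-month difference and δ6 the true 6-month difference. Those lost by month 1 contribute zero.

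| Loss by month 1 | 1-month LOCF estimate (true 10) | Power, LOCF | Power, observed scores | 6-month LOCF estimate, true 0 | 6-month LOCF estimate, true 5 |
|---|---|---|---|---|---|
| 0% | 10.0 | 95.2% | 95.2% | 2.5 | 6.25 |
| 5% | 9.5 | 93.2% | 94.7% | 2.0 | 5.75 |
| 10% | 9.0 | 90.4% | 94.2% | 1.5 | 5.25 |
| 15% | 8.5 | 87.0% | 93.5% | 1.0 | 4.75 |
| 20% | 8.0 | 82.7% | 92.7% | 0.5 | 4.25 |
| 25% | 7.5 | 77.7% | 91.8% | 0.0 | 3.75 |

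Each row is one scenario. The 7.5 points at 1 month and the spurious 2.5 points at 6 months stand at opposite ends of the table, so one 25% monotone loss cannot produce both.

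**Step 4: unequal loss.** The 1-month bias is m_C × gain_C − m_I × gain_I. Suppose controls gain 10 and the intervention arm gains 20 (true difference 10).
- Loss 5% intervention, 25% control: 0.95 × 20 − 0.75 × 10 = 11.5. LOCF inflates the effect.
- Loss 25% intervention, 5% control: 0.75 × 20 − 0.95 × 10 = 5.5. LOCF shrinks it.

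**The case against.** The strongest defence is that the Protocol promises results with and without imputation, so LOCF never stands alone and any distortion would be visible. An SAP that is not shown may also say which result leads. This softens the point. It does not remove it: the Protocol fixes LOCF as the imputation method, and that method is poorly suited to this test schedule whichever result comes first.

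A second defence is that, with equal loss, the bias in the primary outcome runs against the intervention, while the bias that could favour it affects a secondary outcome. That is correct for equal loss. It does not cover unequal loss, which is plausible because the trial cannot be masked and only one arm is asked to use an application.

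A third is that the size is modest if early loss is small. At 10% loss by month 1, power under LOCF is still about 90%. This stands, and it is why a range is shown.

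A reader might infer that the two-level model cannot use any other visit. The Protocol does not support that: the baseline score can enter as a covariate without a third level. What holds is that, as described, the model has no level for repeated scores and so does not analyse the 1- and 6-month scores jointly.

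**Conclusion.** The point holds. The Protocol commits to an imputation rule that assumes no learning in residents missing at 1 month and no change in those missing only at 6 months, and it does not say whether the imputed result is the primary one.

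With equal loss of 0 to 25% at 1 month, a true 10 points is estimated as 10 down to 7.5, with power from about 95% down to 78%. At 6 months a vanished effect appears as between 2.5 and 0 points, depending on how much of the 25% loss falls after month 1. These figures rest on the inferred SD of 20, an SD unchanged by LOCF, balanced baselines, loss unrelated to outcome and an assumed range for 1-month loss.

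A reader might go further and conclude that LOCF always shrinks the primary effect and always creates apparent retention. The documents do not support that. Unequal loss can inflate the 1-month effect. At 6 months, residents missing both tests carry baseline forward, which pulls the other way: with half of the 25% lost by month 1 and a true 6-month effect of 5, the estimate is 0.75 × 5 + 0.125 × 10 = 5.0, with no net bias. The defect is a bias whose size and direction depend on an unknown loss pattern.

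**What to change.** For each guideline, name one primary analysis: a mixed model on observed scores, with teaching unit as a random effect and baseline score included. Two forms would serve:

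- **Preferred:** 1- and 6-month scores as repeated measures within resident, with arm-by-time effects giving both contrasts.
- **Minimum:** the planned two-level model fitted separately at each time point, with baseline score as a covariate.

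Either is valid if data are missing at random given what is in the model. Keep LOCF, if at all, as a labelled sensitivity analysis. A multiple imputation that respects teaching units, with imputed means shifted by stated amounts (delta), would be a useful optional check on departures from missing at random.

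The cost is a change of wording and a little more analysis work. No new data are needed, and the named software can fit these models.

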### Ethical and legal aspects

The trial will fulfill the standards of Good Clinical Practice and the principles of the last Helsinki Declaration (Brazil, 2013). The project has been approved by the Clinical Research Ethics Committee of the Alcorcón Foundation University Hospital in Madrid and the Central Committee for Research of the Primary Care Management of the Community of Madrid. In accordance with Spanish Law 15/1999 on personal data protection, confidentiality and anonymity will be guaranteed both at the execution phase of the trial and during the presentations or publications derived from it.

### Discussion

Teaching units from across Spain will participate in this clinical trial, which anticipates high external outcome validity. Additionally, this intervention might provide information to consider for training in other specialties.

The intervention to be assessed cannot be masked, which could influence its effect. Because there is a possibility of contamination bias among residents, randomization by clusters has been proposed, under the assumption that the number of clusters will be sufficient for each group. Geographic dispersion of the teaching units reduces the possibility of contamination.

Teaching strategies are complex interventions; the design of educational games as an interactive, self-learning application allows for standardization of the intervention.

The considerable variability foreseen between teaching units regarding training in CPGs could imply that some residents have better training with some of these CPGs, which could result in a lack of improvement in these residents' decision-making scores (competency test score). However, this possibility will be adjusted using the training variables of both the teaching units and the residents.

To evaluate the intervention's effectiveness, the primary measurement will take place 1 month after implementation; at this time, our primary objective will be to confirm the effectiveness of the e-learning EDUCAGUIA strategy as a learning tool. Its effect at 6 months after the intervention might not remain, which would lead to a study on the effectiveness of reinforcement interventions. Measuring the primary response at 6 months was considered an option, but the characteristics of training during residency periods make it possible for the residents to acquire the knowledge and abilities of the intervention during rotations or other courses within that time period, thus hindering the isolation of the intervention effect.

Our proposal, which follows the recommendations by the Cochrane review, attempts to overcome the intervention effectiveness measured solely as an increase in knowledge. Therefore, our proposed outcome measure is clinical decision-making in hypothetical scenarios, which is a more realistic approach toward the implementation of guideline recommendations in the decision-making processes of health professionals. Currently, we cannot measure the outcome for all patients being attended by all residents who will receive training for all CPGs. Therefore, our aim is to evaluate at least a representative sample; in the case of recommendations for antibiotic prescription guidelines, we will evaluate the use of computerized clinical records and isolate the decisions of residents and mentors.

The identification of effective teaching strategies will facilitate the incorporation of available knowledge into clinical practice that could eventually improve patient outcomes. The inclusion of information technologies as teaching tools, adapted to training methodologies for adults, permits greater learning autonomy and simultaneously acts as a teaching tool by allowing greater instructor participation in the monitoring and supervision of residents in the relevant knowledge area. The long-term impact of this strategy is unknown; however,

because it is aimed at professionals undergoing training (who must acquire the correct habits and abilities) and it addresses prevalent health problems, a small effect can be of great relevance.

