| d             | Request to Access to training on Educational Games DEMO online by email                                                                                                                                                           |
| 2             | Use of the e-learning EDUCAGUIA application. One month accesible                                                                                                                                                                  |
| e             | GPC recommendations postintervention Competence Test . Outcomes 1 and 6 months.                                                                                                                                                   |

**Fig. 2** Complex intervention pat plot. e-EDUCAGUIA

the last three contests; a teaching plan that includes training on EBM/CPG in the unit; and the number of EBM/CPG training hours in the past year

(b) Resident doctor variables

- Sociodemographic: age, sex, nationality, residency year
- Position in the national exams to access specialty (MIR number); grades obtained in R-1 and R-2 residency years (apt, outstanding, excellent); completion of other specialties; year of obtaining a university degree in medicine; and PhD (yes/no)
- Training: specific training on EBM in the past 5 years and corresponding hours of training, training on critical reading capabilities and corresponding hours of training, having attended formative sessions on how to use CPGs, and corresponding hours of training
- Other variables to achieve secondary objectives: adherence to CPGs, measured as time spent using the application.

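### Differing prior training is to be handled through teaching-unit variables that draw on about 12 unit-level degrees of freedom, while the baseline competence score is not named as a covariate

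*Protocol*

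**What the plan says.** The Discussion expects teaching units to differ considerably in guideline training and fears that already well-trained residents will show little improvement. Its remedy is that "this possibility will be adjusted using the training variables of both the teaching units and the residents".

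The Variables section lists the unit-level candidates. Under unit characteristics it has "a teaching plan that includes training on EBM/CPG in the unit; and the number of EBM/CPG training hours in the past year". For the program director and the technician it has "experience in elaborating guidelines or recommendation, and training in EBM". Counting EBM training separately for director and technician gives four unit-level training variables. Guideline-writing experience could be a fifth.

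The section on competence assessment in both groups provides a baseline test for each guideline before that guideline is presented. The key to Fig. 2 places this test before randomization. The Statistical analysis section uses the baseline score to compare the groups at baseline. It then describes a two-level mixed model (residents within units) for the test score and names no covariates. The Abstract says only that a multilevel regression will serve for adjustment.

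The Sample size section assumes "a relevant post-intervention average difference of 10 points on a 100-point evaluation questionnaire between groups" and works "for an average of 30 residents per teaching unit". It makes no allowance for covariates.

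**The concern.** Allocation is by teaching unit, so the arm is a unit-level variable and its effect is judged against the variation between units. Each unit-level covariate takes one of the same few degrees of freedom and is partly confounded with arm by chance. Such a covariate pays for itself only if it explains enough of the between-unit variance, and at a low ICC there is not much of that to explain.

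The baseline competence score measures what the Discussion worries about, namely what the resident already knows, and it varies mainly between residents. The one adjustment that the protocol promises thus relies partly on the scarcer resource and leaves the more direct measure unnamed. At stake are the precision of the intervention estimate and its dependence on which unit variables happen to be entered.

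**Working it through.** **Reproducing the plan's figure.** The protocol prints "a standard deviation of 0.5" for a 100-point scale. It works only as a standardised effect of 0.5, that is SD = 10/0.5 = 20 points (assumption). Then n = 2 × (1.960 + 1.282)² × (20/10)² = 84 per group, in line with "Assuming an alpha error of 0.05 and a beta error of 0.10, 84 subjects are required for each group". Design effect: 1 + 29 × 0.03 = 1.87. 84 × 1.87 = 157.1, and × 1.25 = 196.4, rounded up to 197 per group, 394 in all.

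**Number of units (inferred).** 394/30 = 13.1. Equal numbers of centers per arm (Randomization) makes this 14, 7 per arm, with 14 − 2 = 12 unit-level degrees of freedom.

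**Variance of a unit mean.** Completers per unit: 30 × 0.75 = 22.5. Total variance 400: between units 0.03 × 400 = 12, within units 388. Unit mean: 12 + 388/22.5 = 29.24. The between-unit share is 12/29.24 = 41%, the most that unit-level covariates can remove.

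**Without covariates.** SE = √(29.24 × 2/7) = 2.89. Noncentrality 10/2.89 = 3.46, t with 12 df (critical value 2.179), power 88.7%.

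**With k unit-level covariates explaining a share R² of the between-unit variance.** The variance becomes 400 × [0.03(1 − R²) + 0.97/22.5], the df are 12 − k, and power is averaged over random draws of independent covariates, so that chance imbalance between arms is included.

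| k | R² = 0 | R² = 0.5 | R² = 1 |
|---|---|---|---|
| 1 | 85.1% | 91.8% | 97.1% |
| 2 | 80.9% | 88.4% | 95.1% |
| 3 | 75.6% | 84.0% | 91.9% |
| 4 | 69.8% | 78.6% | 88.2% |
| 5 | 62.6% | 72.1% | 82.7% |

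**Hand check of the break-even point.** With J = 14 units, chance imbalance inflates the variance of the arm effect on average by (J − 3)/(J − 3 − k) = 11/(11 − k), and the critical value rises as df fall.
- k = 4: 11/7 × (2.306/2.179)² = 1.76. The unit-mean variance must fall to 1/1.76 = 0.568 of its value, so R² = (1 − 0.568)/0.41 = 1.05, which is out of reach.
- k = 2: 11/9 × (2.228/2.179)² = 1.278. 1/1.278 = 0.783, so R² = 0.217/0.41 = 0.53.

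**Sensitivity.**
- ICC 0.052, the top of the protocol's range ("literature shows an ICC of 0–0.052 for similar teaching interventions"): 79.9% without covariates. With four: 59.6%, 72.2% and 88.7% at R² = 0, 0.5 and 1, breaking even at about 0.75.
- 20 units with 14.8 completers each, ICC 0.03: 92.7% without covariates. With four: 83.6%, 89.1% and 93.9%.
- 14 units with all 30 residents retained, ICC 0.03: four covariates break even at R² = 0.92.

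**Baseline score instead.** Let r be the within-unit correlation of baseline and follow-up score. The documents give no value, so 0.3 to 0.7 is assumed. Unit-mean variance = 12 + 388(1 − r²)/22.5, still on about 12 df.
- r = 0.3: 27.69, power 90.3%.
- r = 0.5: 24.93, power 93.0%.
- r = 0.7: 20.79, power 96.4%.

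This credits the baseline score with none of the between-unit variance.

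**The case against.** The protocol fixes neither the number of units nor the number of covariates. All Spanish teaching units are to be invited, so there may be more than 14. The Discussion sentence does not say that all four variables enter together: only two stand under unit characteristics, and the rest are listed with the staff's personal data. A covariate list is commonly left to the statistical analysis plan. The adjustment is offered to deal with prior training, not to gain power. All of this stands.

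A reader might therefore infer too much:
- **That the promised adjustment uses up the unit-level degrees of freedom.** Two covariates leave 10 of 12.
- **That it can at best break even.** This is true of four at ICC 0.03 with 22.5 completers. It is not true of one to three, nor of four at ICC 0.052.
- **That it usually loses power.** That needs a distribution for R², and the documents give none. The variability that the authors foresee, if anything, suggests that they expect these variables to matter.
- **That it makes the primary estimate less precise.** The Statistical analysis section gives both a t test and a mixed model and does not say which covariates enter either.

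The calculation also uses unit means with independent normal covariates. The real ones are partly categorical and probably correlated.

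None of this touches the comparison with the baseline score. It is already collected, it measures prior competence directly, and it hardly draws on the unit-level degrees of freedom.

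**Conclusion.** The point holds in a conditional form. With about 14 units, SD 20, ICC 0.03 and 22.5 completers per unit, entering all four listed unit-level training variables cannot lift power above the unadjusted 89%. The cost runs from under 1 point if they explain all of the between-unit variance to 19 points if they explain none. Two break even at about half. Fewer covariates, more units or a higher ICC can turn the loss into a gain.

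What does not depend on the number of covariates is the missed opportunity. Under the same assumptions, adjusting for the resident's baseline score adds about 2 to 8 power points for an assumed within-unit correlation of 0.3 to 0.7, and it serves the purpose given in the Discussion more directly. The analysis plan, which is not at hand, may already include it. The protocol names the training variables only.

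**What to change.** - Adjust the primary two-level model for the resident's baseline competence score on the guideline concerned, with resident-level training variables if wanted.
- Keep any unit-level training covariates in the primary model few and name them in advance. No exact cap follows from the figures: one or two can help if they are strongly prognostic.
- Put the remaining unit-level training variables in a sensitivity analysis.
- Reword the Discussion sentence to match.

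This changes wording only and needs no new data. The downside is that a chance imbalance in unit-level training is then handled mainly through the baseline scores and the sensitivity analysis.
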